## Abstract

**Background:**

Daily stressors are associated with cognitive decline and increased risk of heart disease, depression, and other debilitating chronic illnesses in midlife adults. Daily stressors tend to occur at home or at work and are more frequent in urban versus rural settings. Conversely, spending time in natural environments such as parks or forests, or even viewing nature-themed images in a lab setting, is associated with lower levels of perceived stress and is hypothesized to be a strong stress “buffer,” reducing perceived stress even after leaving the natural setting. However, many studies of daily stress have not captured environmental contexts and relied on end-of-day recall instead of in-the-moment data capture. With new technology, these limitations can be addressed to enhance knowledge of the daily stress experience.

**Objective:**

We propose to use our novel custom-built Stress Reports in Variable Environments (STRIVE) ecological momentary assessment mobile phone app to measure the experience of daily stress of midlife adults in free-living conditions. Using our app to capture data in real time will allow us to determine (1) where and when daily stress occurs for midlife adults, (2) whether midlife adults’ daily stressors are linked to certain elements of the built and natural environment, and (3) how ecological momentary assessment measurement of daily stress is similar to and different from a modified version of the popular Daily Inventory of Stressful Events measurement tool that captures end-of-day stress reports (used in the Midlife in the United States [MIDUS] survey).

**Methods:**

We will enroll a total of 150 midlife adults living in greater Indianapolis, Indiana, in this study on a rolling basis for 3-week periods. As those in underrepresented minority groups and low-income areas have previously been found to experience greater levels of stress, we will use stratified sampling to ensure that half of our study sample is composed of underrepresented minorities (eg, Black, American Indian, Hispanic, or Native Pacific Islanders) and approximately one-third of our sample falls within low-, middle-, and high-income brackets.

**Results:**

This project is funded by the National Institute on Aging from December 2022 to November 2024. Participant enrollment began in August 2023 and is expected to finish in July 2024. Data will be spatiotemporally analyzed to determine where and when stress occurs for midlife adults. Pictures of stressful environments will be qualitatively analyzed to determine the common elements of stressful environments. Data collected by the STRIVE app will be compared with retrospective Daily Inventory of Stressful Events data.

**Conclusions:**

Completing this study will expand our understanding of midlife adults’ experience of stress in free-living conditions and pave the way for data-driven individual and community-based intervention designs to promote health and well-being in midlife adults.

**International Registered Report Identifier (IRRID):**

DERR1-10.2196/51845

## Introduction

Daily stressors are associated with cognitive decline and increased risk of heart disease, depression, and other debilitating chronic illnesses for midlife adults [1-5]. Daily stressors tend to occur at home or at work and are more frequent in urban versus rural settings [6-8]. Conversely, spending time in natural environments such as parks or forests, or even viewing nature-themed images in a lab setting, is associated with lower levels of perceived stress and is hypothesized to be a strong stress “buffer,” reducing perceived stress even after leaving the natural setting [9-12]. The role that natural environments can play in reducing stress arousal is particularly important when considering that neighborhoods with high poverty rates and higher proportions of racial or ethnic minorities have less access to green space and higher exposure to stressful elements such as abandoned buildings and crime [13-15]. However, many studies of daily stress have not captured environmental contexts and relied on end-of-day recall instead of in-the-moment data capture. With new technology, these limitations can be addressed to enhance knowledge of the daily stress experience [16].

In the United States, midlife adults are staying in the workforce longer and are engaging in higher levels of physical activity than previous generations, potentially extending their interactions with elements of the built and natural environments that influence their experience of daily stress [17,18]. Recent evidence has revealed that age-related linear increases in perceptions of well-being observed during past periods of economic prosperity have not continued during more recent, less economically prosperous times [19]. The seismic and unpredictable economic and social changes brought about by the COVID-19 pandemic have greatly altered the experience of daily stressors in the built and natural environment, a trend that is likely to continue well into the future [20].

In the midlife adult population, stress (or the lack thereof) plays an important role in the aging process. The relationship between various types of stress and alterations in cognitive functioning has been well documented, and there is growing evidence showing a relationship between daily stress in midlife and cognitive decline [2,3,21]. Perceived stress in midlife adults has also been closely linked with physical disability later in life [22,23]. A growing body of research has also found that perceived stress, particularly in the workplace, is closely related to heart disease [24]. Furthermore, while individual health and wellness in midlife is no doubt important, longitudinal studies have shown that the health and wellness of midlife adults is also pivotal to others in their workplace, society in general, and in the lives of those in younger and older generations who often are socioeconomically dependent on midlife family members [25].

Midlife adults of different socioeconomic statuses and races are subject to structural inequality in their living environments. Those living in urban environments with higher levels of poverty and violence experience higher levels of environmental stress than those living in suburban or rural environments [15]. In particular, it is well documented that underrepresented minorities are exposed to environmental stressors more than nonunderrepresented minorities [26,27]. One explanation for racial differences in exposure to stressors is residential segregation, resulting in a predisposition for low-income minorities’ exposure to environmental stressors such as traumatic events, urban decay, and poverty [28]. Minority and low-income midlife adults’ exposure to environmental stressors has been linked to unhealthy behaviors like cigarette smoking [29], as well as myriad negative health outcomes [30].

In response to this research gap, we propose to use our novel custom-built Stress Reports in Variable Environments (STRIVE) ecological momentary assessment (EMA) mobile phone app to measure the experience of daily stress of midlife adults in free-living conditions. Using our app to capture data in real time will allow us to determine (1) where and when daily stress occurs for midlife adults, (2) whether midlife adults’ daily stressors are linked to certain elements of the built and natural environment, and (3) how EMA measurement of daily stress is similar to and different from a modified version of the popular Daily Inventory of Stressful Events (DISE) measurement tool that captures end-of-day stress reports (used in the Midlife in the United States [MIDUS] survey) [31].

Completing this study will expand our understanding of mid-life adults’ experience of stress in free-living conditions and pave the way for data-driven individual and community-based intervention designs to promote health and well-being in midlife adults. Potential interventions that could stem from our data include technology-based “just-in-time” interventions that account for spatiotemporal location, mindfulness-based interventions that incorporate environmental stress triggers, and community-based interventions designed to eliminate environmental stressors that are commonly experienced by midlife adults (eg, congested areas).

## Methods

### Overview

In this stage 0 (of the NIH Stage Model for behavioral intervention development) study, we propose an interdisciplinary mixed method approach to examine the occurrence of daily stressors in the moment they occur for midlife adults in the built and natural environment using mobile and wearable technology. A total of 150 midlife adults will be enrolled in this study on a rolling basis for 3-week periods. Participants will meet with a researcher in person at the start and end of their 3-week study period. They will be provided with a smartphone preloaded with the STRIVE app and a Polar Unite smartwatch. They will be instructed to carry the phone and wear the watch for the 3-week duration of the study. Each enrolled participant will use one or more daily stress measurement tools in any given week, randomized to account for participant priming. In 1 week of participation, participants will complete the DISE by the Research Electronic Data Capture (REDCap; Vanderbilt University) survey every evening. In another week of participation, participants will use the STRIVE app to report daily stressors in real time and complete the DISE every evening. In another week of participation, participants will only report stressors in real time through the STRIVE app. Automated SMS text messages will be sent to participants each day to remind them of what they need to do to remain active in the study and provide survey links when needed.

Participants will be recruited from the greater Indianapolis area in Indiana. As those in underrepresented minority groups and low-income areas have previously been found to experience greater levels of stress, we will use stratified sampling to obtain a sample that is racially and socioeconomically diverse (Table 1). Income levels are defined as the bottom, middle, and top third of household incomes based on 2020 US Census percentiles (low income: <US $39,535; middle income: US $39,535-$85,076; high income: >US $85,076) [32]. Participants will be recruited with the assistance of the Indiana Clinical and Translational Sciences Institute recruitment concierge services and their community partnerships. Recruitment materials will be posted on community-based social media pages, on paper flyers in public community spaces, and through all communication channels operated by community health partners.

**Table 1 table1:** Study sample stratified by race and household income (N=150).

Race	Low income, n (%)	Middle income, n (%)	High income, n (%)
Black, American Indian, Hispanic, Native Pacific Islanders	25 (16.6)	25 (16.6)	25 (16.6)
White or Asian	25 (16.6)	25 (16.6)	25 (16.6)

### Measurement of Stress With the STRIVE App

Study participants will be asked to carry the researcher’s provided Android mobile phone with them at all times. The STRIVE app passively records the participant’s GPS coordinates every 60 seconds throughout the data collection period (Table 2). Research participants are informed that their location is being tracked by the app. When participants experience a daily stressor, they are asked to open the app and provide a rating of their stress level, a description of the stressor, their preferred coping strategy, and optionally take a photograph of the environment where they experienced stress (Figure 1). Data input is kept to a minimum to reduce participant burden and burnout [33].

**Table 2 table2:** All study measures.

Measurement tools			Measure
**Pretest survey**			
	CDC^a^ Healthy Days [34]	Overall health	
	Godin Leisure-Time Exercise Questionnaire [35]	Physical activity level	
	Portion of Behavioral Risk Factor Surveillance (BRFSS) [36]	Substance use and abuse	
	Social Provisions Scale [37]	Social support	
	UCLA^b^ Loneliness Scale [38]	Loneliness	
	Patient Health Questionnaire-9 (PHQ-9) [39]	Depressive symptoms	
	Adverse Childhood Events Scale (ACES) [40]	Early life stress	
	Economic Strain Model [41]	Financial strain	
	Neighborhood Disorder Scale [42]	Neighborhood safety	
**Real time measurements (all time-stamped)^c^**			
	STRIVE^d^ app	Per 60 second GPS coordinates (continuous) Self-reported stress level (7-point scale) Self-reported stressor (text-based) Self-reported coping response (text-based) Photo of stressful environment (JPEG)	
	Polar Unite Smartwatch	Heart rate (continuous) Activity level (continuous)	
End-of-day recall DISE^e^ measurements^c^			Self-reported overall stress level (7-point scale) Self-reported stressor type Self-reported stress level by stressor (7-point scale) Self-reported date

^a^CDC: Centers for Disease Control and Prevention.

^b^UCLA: University of California, Los Angeles.

^c^Additional measurements include demographics and health history.

^d^STRIVE: Stress Reports in Variable Environments.

^e^DISE: Daily Inventory of Stressful Events.

**Figure 1 figure1:**
[figure not shown]
The Stress Reports in Variable Environments (STRIVE) app.

We have created a protocol to promote the safety of research participants during their reporting of daily stressors with the STRIVE app. If they cognitively appraise themselves as stressed and are in a situation in which it is unsafe to use their phones (eg, driving a car), they are asked to proceed to the nearest safe location before recording their experience. Participants will be asked to indicate when and where the stressor occurred if they are not reporting from the location in which the stress occurred in their later description of it. Many people go through a day without experiencing a stressor [43]; for days when this is the case, participants will be asked to indicate on their app that they had not experienced stress but were still actively participating in the study.

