### Ethics Approval

This study has been approved by the Indiana University Institutional Review Board (study number 1910712088). Informed consent has been and will be obtained from all research participants. A special document outlining when and where it is appropriate and safe to take photographs of stressful environments will be provided to all research participants, with a focus on protecting the privacy of others. Further, a document highlighting that study participants are not to report stressors in dangerous situations (eg, while driving a car) will be provided. Although we will make efforts to deidentify study data as much as possible, certain elements of data collected (eg, pictures and GPS coordinates) could be used to identify participants. Participants are informed of this risk and may choose not to report stressors or take pictures in situations where they are concerned about their confidentiality. Each study participant will be paid US $150 for their participation in the study.

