## Results

This study will take approximately 24 months to complete and will take place between December 2022 and November 2024. Enrollment began in August 2023 and is expected to be completed by July 2024. We expect the following study findings:

A better understanding of where and when stressors occur for midlife adults in free-living conditions. We hypothesize that the quantity of stressors reported, type of stressors reported, and subjective severity of stressors reported by midlife adults will differ by location (eg, at home vs at a park) and time (eg, morning vs evening) throughout the built and natural environment.An understanding of specific elements of the built and natural environment that contribute to midlife adults’ daily stress. We hypothesize that distinct environmental characteristics (eg, abandoned buildings) will emerge as contributors to stress through the qualitative analysis of stressor descriptions and pictures of stressful environments.An understanding of how the STRIVE-based EMA of daily stress is supplementary or complementary to the DISE. We hypothesize that, when reporting through the STRIVE app compared with when reporting through the DISE, midlife adults will report a greater number of daily stressors, a lower average stressor severity, and different types of stressors.

Throughout the study, we will present our research findings at relevant academic or professional conferences and publish peer-reviewed papers. We will also share our study findings with partner governmental organizations and nongovernmental organizations in the state of Indiana. These organizations will likely find our data useful for future community planning.

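### The stressor's time is asked for only after a change of place, so a late report from the same place keeps its entry time and its time of day may be misclassified

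*Protocol article*

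**What the plan says.** The protocol article intends reporting in the moment. Under Measurement of Stress With the STRIVE App: "When participants experience a daily stressor, they are asked to open the app and provide a rating of their stress level". Table 2 groups the STRIVE items under "Real time measurements (all time-stamped"). They are GPS position, stress level, stressor text, coping text and photograph. No item for the time of the stressor is listed.

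The same section foresees one reason for delay, a situation in which using the phone is unsafe. Participants then move first: "they are asked to proceed to the nearest safe location before recording their experience". Ethics Approval repeats the restriction: "study participants are not to report stressors in dangerous situations (eg, while driving a car"). For reports made elsewhere, participants are asked to "indicate when and where the stressor occurred if they are not reporting from the location in which the stress occurred", and they give this "in their later description of it".

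The first expected finding in Results is that the number, type and severity of stressors "will differ by location (eg, at home vs at a park) and time (eg, morning vs evening"). Geospatial Analysis fits a model with temporal, spatial and spatiotemporal effects, and includes heart rate and activity from the watch.

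**The concern.** A time stamp records when the entry was made. It equals the time of the stressor only if the participant reports at once. The article's only correction depends on having moved, so a late report from the same place falls outside it.

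This form of delay is easy to foresee. The Introduction states: "Daily stressors tend to occur at home or at work and are more frequent in urban versus rural settings". Home and work are places where people stay or to which they return. Reporting depends on the participant opening the app, and two features could prompt catching up: the daily text-message reminders, and, in the week that combines both tools, the evening DISE question on how often the participant felt stressed. Both are inferences. The article gives no hour for the reminders and does not say that they invite back-reporting.

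At stake are the when part of the first objective, the morning-versus-evening contrast, any place-by-time effect (home and work being the most exposed places), and the hour of heart-rate and activity data set against a report. Place itself is not at risk in this case, because the participant is where the stressor happened.

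**Working it through.** The article states no figure on this point, so there is nothing to reproduce. The check has two parts.

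**1. The rule, case by case**

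| Report | Occurrence time requested, as described? | Time available |
|---|---|---|
| As the stressor happens | Not needed | Entry stamp, correct |
| Late, from another place | Yes, in the description | Stated time |
| Late, from the same place | No | Entry stamp only, unless volunteered in free text |

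The third row is the gap. Table 2 does not close it: it lists a self-reported date for the DISE but no stressor time for STRIVE.

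**2. How much it could matter (illustration; every input is assumed)**

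*Same-day delay.* Take two 8-hour periods with stressors spread evenly within each. A share f of reports is entered d hours late at the same place, and later-period reports stay in their period. A late report crosses the boundary only if the stressor fell in the last d hours of the earlier period, so the share of earlier-period stressors stamped in the later one is m = f × d / 8. With a true later-to-earlier ratio R, the observed ratio is (R + m) / (1 − m).

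| f | d (hours) | m | Observed, R = 1 | Observed, R = 0.8 |
|---|---|---|---|---|
| 5% | 0.25 | 0.0016 | 1.003 | 0.803 |
| 10% | 1 | 0.0125 | 1.025 | 0.823 |
| 20% | 2 | 0.05 | 1.05/0.95 = 1.105 | 0.85/0.95 = 0.895 |
| 20% | 4 | 0.10 | 1.10/0.90 = 1.222 | 0.90/0.90 = 1.000 |
| 30% | 4 | 0.15 | 1.15/0.85 = 1.353 | 0.95/0.85 = 1.118 |

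Short or rare delays do almost nothing. Long and common ones can remove or reverse a true difference.

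*Same-day and overnight delay together.* Of 100 stressors, let 60 occur before evening and 40 in the evening, a true ratio of 1.50. Let p be the share of the 60 entered that evening at the same place, and q the share of the 40 entered the next morning at the same place. Observed ratio = [60(1 − p) + 40q] / [40(1 − q) + 60p].

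- p = 0.10, q = 0: 54/46 = 1.17
- p = 0.10, q = 0.15: (54 + 6)/(34 + 6) = 1.50, no net bias
- p = 0.05, q = 0.15: (57 + 6)/(34 + 3) = 1.70, bias the other way

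The two flows cancel whenever 60p = 40q. With q = 0 the ratio reaches 1 at p = 1/6. Here p counts only reports that are late, from the same place and across the boundary. In the 8-hour model, m = 1/6 needs f × d = 8/6, for example a third of all reports entered 4 hours late.

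**The case against.** The strongest reply is that the design already deals with timing. Participants are told to report when the stressor is experienced, and the app question quoted under Qualitative Analysis is in the present tense. The one delay the article allows for, an unsafe situation, is handled by moving and then stating time and place. On this view, late entry from the same place is a departure from the instruction, as in any self-initiated diary. Also, the app screen in Figure 1 was not visible in the text reviewed, so a field for the time of the stressor cannot be ruled out, and free-text descriptions may reveal that an event is past.

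Much of this stands. It rules out three stronger readings that a reader might draw:

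- *That the morning-versus-evening result is wrong.* The article gives no delay rate or length, and a delay matters for this contrast only if it crosses a period boundary.
- *That the bias always runs towards evening.* Each entry follows its event, but an evening stressor entered the next morning is counted as a morning one, so net direction is open.
- *That late reports can never be recognised.* Some descriptions will give them away, although nothing ensures it.

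The reply does not remove the gap. The article does provide for reports that are not immediate, and it makes the request for time depend on place when the relevant condition is delay.

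**Conclusion.** The point holds as a limited flaw in a stated data-capture rule. As described, late reports from the same place carry only their entry time, and their time of day may be misclassified. Under the assumed same-day delays the effect on a true ratio of 1 runs from 1.003 to 1.353, that is, from negligible to material. With overnight delay the bias may cancel or change sign. A claim that the finding would reverse once about 17% of earlier stressors are moved is not supported: it rests on an assumed 60/40 split with no overnight flow. The conclusion assumes that the app has no field for occurrence time beyond what the text and Table 2 describe. The change is worth making because it is small, it protects the first objective, and occurrence times not collected cannot be reliably recovered later.

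**What to change.** Make delay the trigger. Each STRIVE report not made as the stressor happens should state when it occurred, whether or not the participant has moved. Use the stated time in the time-of-day analysis and to select the GPS, heart-rate and activity records. Mark reports as real time or late, and repeat the analysis on the real-time ones. The instructions on safe reporting are unaffected.

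For participants enrolled under the present instruction, keep the entry time and report results separately by instruction version as a sensitivity analysis. State plainly that a version indicator does not correct times already misstamped and, with rolling enrolment from August 2023 to July 2024, is confounded with calendar time.

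The cost is one line in the instructions, one short entry on late reports (against the stated aim of keeping input to a minimum), and a change of instruction during enrolment. If the app screen already has such a field, it is enough to state that it is used for all late reports and that the analysis uses it.
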